## Abstract

**Background:**

Androgen deprivation therapy (ADT) for prostate cancer is associated with adverse cardiometabolic effects such as reduced libido, hot flashes, metabolic syndrome, diabetes, myocardial infarction, and stroke. This reduces quality of life and potentially increases mortality. Several large clinical trials have demonstrated improvements in cardiometabolic risk with comprehensive multimodality lifestyle modification. However, there is a lack of data for such interventions in men on ADT for prostate cancer, and existing studies have used non-standardized interventions or lacked data on metabolic risk factors.

**Objective:**

The Comprehensive Lifestyle Improvement Project for Prostate Cancer (CLIPP) is designed to address these gaps by using an intervention modeled on the Diabetes Prevention Program, a standardized multicomponent intervention with demonstrated effectiveness in reducing cardiometabolic risk factors that has been successfully adapted for multiple disease types including breast cancer.

**Methods:**

A single-arm unblinded clinical trial will be conducted to determine the feasibility of conducting a 24-week comprehensive lifestyle modification intervention that targets weight loss and increased physical activity modeled on the Diabetes Prevention Program in 30 men on ADT for prostate cancer. Secondary aims are to determine the effect of the intervention on cardiometabolic markers and quality of life. The tertiary aim is to determine the effect of the intervention on markers of inflammation and angiogenesis, important mechanisms for prostate cancer progression. Participants will be recruited from the University of Arizona Cancer Center and the surrounding community. The intervention will be delivered weekly in person and over the phone for 16 weeks. For Weeks 16-24, participants receive weekly phone calls from the study health coach to motivate them to continue their lifestyle modification. Questionnaire and biological data are collected at baseline, 12 weeks, and 24 weeks. Body composition using dual-energy x-ray absorptiometry scans will be performed at baseline and end of study.

**Results:**

Based on a sample size of 30, the two-sided 95% confidence interval will not be wider than 0.373 standard deviations for the adherence rate and will not be wider than 0.374 for the retention rate. In addition, the study will have a power of 80% to detect a change of 0.47 standard deviations from baseline for each of the markers investigated in the secondary and tertiary aims assuming a within-subject correlation of 0.20 at a significance level of 5%. The recruitment period is from October 2018 to April 2019.

**Conclusions:**

The aim of CLIPP is to determine the feasibility of conducting a Diabetes Prevention Program–style comprehensive lifestyle modification intervention in men with ADT for prostate cancer and its effects on cardiometabolic adverse effects, quality of life, as well as markers of inflammation and angiogenesis. Results will inform the development of future clinical trials in this population.

**International Registered Report Identifier (IRRID):**

DERR1-10.2196/12579

## Introduction

Androgen deprivation therapy (ADT) has been demonstrated to improve disease-free survival and overall survival in men with prostate cancer (PCa) [1,2]. Androgen deprivation can be accomplished through surgical castration (bilateral orchiectomy) or medical castration through gonadotropin-releasing hormone (GnRH) agonist and antagonist as well as antiandrogen medication [3,4]. Changed hormonal milieu due to ADT is associated with a number of adverse effects such as metabolic syndrome, weight gain, decreased libido, insulin resistance, obesity, sarcopenia, as well as diabetes, myocardial infarction, and cerebrovascular events. These adverse effects not only lower the individual’s quality of life (QoL) but also contribute to increased mortality [3,5,6]. Reports by Cheung and Alibhai demonstrate that ADT is associated with clinically significant decreased QoL especially in the physical and sexual domains [5,6]. In a meta-analysis by Bosco et al, relative risk (RR) for any type of nonfatal cardiovascular disease was 1.38 (95% CI 1.29-1.48) for men with PCa on GnRH agonists, compared with men not treated with ADT [3]. The associations between GnRH agonists and myocardial infarction or stroke were even stronger: RR 1.57 (95% CI 1.26-1.94) and RR 1.51 (95% CI 1.24-1.84), respectively [3].

Comprehensive multicomponent lifestyle modification interventions have demonstrated improvement in metabolic profile and cardiovascular risk factors [7]. The Diabetes Prevention Program (DPP) was a randomized clinical trial (N=3234) comparing the effect of intensive multicomponent lifestyle modification, metformin, or placebo on development of diabetes in persons with impaired glucose tolerance [7]. In this trial, the incidence of diabetes was 11.0, 7.8, and 4.8 cases per 100 person-years for placebo, metformin, and lifestyle modification, respectively. Compared to placebo, incidence of diabetes was reduced by 58% in the lifestyle arm and 31% in the metformin arm. Although there was slight attenuation of the effect, the incidence of diabetes was still lower in the lifestyle arm as compared to the metformin arm (34% and 18%, respectively) after 10 years of follow-up [8]. The 10-year follow-up demonstrated major reductions for blood pressure (systolic, 2-3 mmHg and diastolic, 5-6 mmHg), low-density lipoprotein cholesterol (0.47-0.54 mmol/l), and triglycerides (0.18-0.32 mmol/l) as well as increases in high-density lipoprotein (0.13-0.16 mmol/l) for all the three groups, whereas hyperlipidemia (*P*<.012), hypertension (*P*<.09) [9], and medication use was lower for the lifestyle group. Lack of differentiation between the three groups could potentially be due to all three groups’ receiving the lifestyle intervention when the primary clinical trial ended. The DPP has been successfully adapted for breast cancer patients [10]. In the Lifestyle Exercise And Nutrition (LEAN) study, 100 women with breast cancer were randomized to in-person or phone-based lifestyle modification or usual care. There was a statistically significant decrease in weight (*P*=.004 and *P*=.009 for in-person or phone-based intervention) compared to usual care. Additionally, women who lost >5% weight demonstrated significant improvements in metabolic (insulin and leptin, *P*=.05 and .002, respectively) and inflammatory (C-reactive protein and interleukin-6, *P*=.02 for both) markers [10]. These data served as the premise for the ongoing Breast Cancer Weight Loss trial of a DPP-modified intervention for weight loss in breast cancer survivors [11].

Interventions addressing either exercise or nutrition have demonstrated benefit in men on ADT for PCa [12]. However, there is a lack of data with respect to comprehensive multicomponent standardized lifestyle improvement programs. Recently published results from the Individualized Diet and Exercise Adherence-Pilot (IDEA-P) trial demonstrated that a multicomponent lifestyle modification program is effective in improving mobility performance (*P*<.02), muscular strength (*P*<.01), body fat percentage (*P*<.05), and fat mass (*P*<.03) [13]. However, cardiometabolic risk factors or QoL were not outcome variables in this paper nor was a standardized intervention like the DPP used in the study.

Obesity is an important risk factor for not only cardiometabolic diseases but also for PCa progression. As many as 77% men diagnosed with PCa can be classified as overweight or obese, which is higher than the national average [14]. Obesity has been associated with PCa aggressiveness, progression, and cancer-specific mortality [15]. The Continuous Update Project report on PCa identifies overweight and obesity to be strong risk factors for PCa progression [16]. Hence, an intervention like the DPP with proven efficacy towards reducing weight and improving cardiometabolic risk factors could be hypothesized to have the same effect in men on ADT for PCa.

The current trial addresses the above-mentioned deficiencies by conducting a feasibility and early efficacy study to determine the utility of a DPP-style lifestyle modification intervention on cardiometabolic risk factors and QoL in men on ADT for PCa. Additionally, the effect of the intervention on markers of inflammation and angiogenesis will be determined to understand its impact on PCa progression, as inflammation and angiogenesis are important mechanisms for PCa progression [17-21].

## Methods

### Study Design

The aims of the Comprehensive Lifestyle Improvement Program for Prostate Cancer (CLIPP), a single-arm unblinded clinical trial, are to determine (1) the feasibility of conducting a 24-week comprehensive lifestyle modification intervention in men on ADT for PCa, (2) the effect of a comprehensive lifestyle modification on cardiometabolic risk factors and QoL in men on ADT for PCa, and (3) the effect of a comprehensive lifestyle modification on markers of inflammation and angiogenesis. Regulatory approval for this project has been obtained from the University of Arizona Institutional Review Board and its affiliated hospital system, Banner University Medical Center. Thirty subjects will be recruited from the University of Arizona Cancer Center (UACC), a National Cancer Institute–designated Comprehensive Cancer Center located in Tucson, Arizona, and its surrounding community. The UACC Cancer Survivorship Clinic, Genitourinary Oncology Clinic, and Radiation Oncology Clinic will be involved in recruitment. Flyers will be distributed at various locations around the cancer center informing potential participants about the study. Principal investigators and study staff will reach out to various prostate cancer support groups around the city to recruit participants. Principal investigators and collaborators will introduce the study to potential participants. If the potential participant is willing to participate, their information will be shared with the clinical research associate who will determine eligibility via telephone. Participants recruited through other methods will be instructed to call the clinical research associate directly for timely screening. After eligibility screening, the associate will explain the study purpose, answer questions, and ascertain interest in participation. If the participant agrees, informed consent will be obtained.

### Eligibility

To be eligible for this study, participants are required to meet the following inclusion and exclusion criteria. Since this is a feasibility trial, criteria are purposefully broad. Participants must (1) be men diagnosed with prostate cancer (Stage I-III) within the past 10 years, who are on ADT for their disease, (2) be age 40 or older with at least a 5-year life expectancy, (3) be willing to participate in a lifestyle modification intervention, including all assessments and measurements, (4) speak English, and (5) if participating in any other clinical trial participants, have a 30-day washout period before they can become eligible for this trial. The exclusion criteria for the study consist of the following: (1) PCa survivors currently participating in any other clinical trials, (2) PCa survivors on hospice or with a life expectancy less than 5 years, (3) survivors with Stage IV PCa, (4) having digestive diseases (eg, inflammatory bowel disease, diverticulitis) that make for intolerance of significant increases in plant food intake, and (5) individuals unable to fully comprehend the informed consent or other procedural requirements. Individuals with high adherence to lifestyle guidelines (eg, consuming a vegan diet or participating in moderate to vigorous physical activity for >45 minutes/day, 7 days/week) will be excluded.

### Informed Consent

The investigational nature and objectives of the trial, the procedures, and interventions involved and their attendant risks and discomforts, and potential alternative therapies will be carefully explained to subjects and a signed informed consent obtained. The informed consent form approved by the University of Arizona Institutional Review Board will be used for this. Documentation of informed consent for screening will be maintained in the subject’s research file.

### Study Procedure

Participants will be scheduled for a baseline visit after informed consent has been obtained. This visit will consist of obtaining anthropometric measures, questionnaire data, biological samples, and body composition data using dual-energy absorptiometry (DXA) scan. The intervention will be initiated at this visit. Participants will be provided with a fitness tracking device (FitBit Charge2) that will support the tracking of fitness goals and provides the study team with physical activity data. Participants will keep the fitness tracker after completion of study. Participants will be followed weekly for a duration of 24 weeks. Baseline and every fourth visit will be in-person, whereas the remainder of the intervention support will be provided over the phone. This delivery strategy was adopted based on results of focus group discussions conducted with PCa survivors at the UACC regarding their interests in participating in a lifestyle modification intervention [22]. Anthropometric measurements will be collected at each in-person visit. Questionnaire data and biological samples will be collected at baseline, 12 weeks, and 24 weeks. DXA scans will be obtained at baseline and end of study (24 weeks) to assess body composition changes over time. An exit survey will be carried out at the end of the study to assess acceptance and feasibility including an understanding of their experience and suggestions for improvement. A similar survey will be carried out if the participant decides to terminate their participation earlier than study completion. See Multimedia Appendix 1 for the study timeline.

### Intervention

The intervention has been modeled on the DPP and adapted for men with PCa. The goals of the intervention are to help participants (1) achieve and maintain 7% weight loss from their starting weight (if participant body mass index [BMI] is >25) and (2) achieve and maintain 150 minutes of moderate intensity physical activity weekly. If participant BMI is <25 or if they are already engaging in 150 minutes of moderate intensity physical activity weekly, the goal will be to maintain that for the duration of the trial. The 16-week curriculum covering nutrition, physical activity, as well as supportive strategies to promote and maintain behavior modification was designed to help the participants achieve these goals [7]. Topics covered during the weekly sessions are listed in Figure 1. The curriculum will be taught by an experienced health coach trained by a DPP principal investigator and master trainer. After completion of the curriculum-based intervention, participants will be followed for 8 weeks. During this time, participants will receive weekly calls from the health coach aimed at maintaining motivation and problem solving as well as behavioral goal maintenance. The fundamental components of the intervention are based on social cognitive theory, the theory of planned behavior, and the transtheoretical model [23].

**Figure 1 figure1:**
[figure not shown]
Intervention details.

### Outcome Measures

#### Feasibility Measures

Aim 1 of this study is to determine feasibility and hence the outcome measures for this aim will be recruitment, retention, and maintaining protocol adherence by the participants. The recruitment goal is set at 30 participants recruited over a 6-month period. The retention goal is set at 80%, and the adherence goal is set at 75% participation. If 80% (24/30) of participants complete the trial, the retention goal for this trial will be achieved. If participants attend 75% of the intervention delivery visits (in-person and phone combined), they will be considered adherent to the protocol.

#### Efficacy Measures

For Aim 2, anthropometric measures (ie, height in inches, weight in pounds, waist and hip circumference in inches) and blood pressure (ie, systolic and diastolic mm of hg) will be carried out by the same, trained study personnel for all participants at all visits, using established protocols. This will ensure consistency between measurements and reduction in error. Serum samples for metabolic markers (ie, fasting glucose, hemoglobin A1C, lipid panel) will be collected and sent to a certified clinical laboratory. We will determine QoL using standardized and validated questionnaires. The Patient Reported Outcomes Measurement Information System (PROMIS) global physical and mental health scale will be used to determine the overall quality of life, whereas the Expanded Prostate Cancer Index Composite Short Form (EPIC-26) will be used to assess disease-specific QoL. Preliminary efficacy will be established if the intervention results in a significant decrease in body weight, body fat, and metabolic indices as well as improvement in general and disease-specific QoL over the course of the trial (24 weeks). For Aim 3, serum collected at baseline, 12 weeks, and 24 weeks will be processed for markers of inflammation (ie, Interleukin-6, Interleukin 1-beta, Interleukin-8, stromal cell derived factor 1-alpha, and basic fibroblast growth factor) and angiogenesis (ie, vascular endothelial growth factor and plasma placental growth factor) using enzyme linked immunosorbent assay (ELISA). Kits will be purchased from Meso Scale Discovery (Rockville, MD) and R&D Systems (Minneapolis, MN). Prior literature demonstrates changes in these markers due to ADT [4], hence, the reason for choosing these markers.

#### Ancillary Measures

In addition to the outcome measures mentioned above, ancillary measures will also be collected that will be used for correlative analyses in the future. Other ancillary measures will consist of Pittsburgh Sleep Quality Index to assess sleep quality, Arizona Food Frequency Questionnaire to assess food patterns, DXA scans for body composition assessment, and urine samples. Questionnaires and urine samples will be collected at baseline, 12 weeks, and 24 weeks and stored for future analyses. DXA scans will be conducted at baseline and end of study. Extra serum samples will also be stored in -80°Celsius freezers for future use. The samples will be housed in the central freezer facility of the University of Arizona Cancer Center, which is monitored through a 24-hour alarm system.

### Statistical Considerations

#### Statistical Analysis

The primary aim of this study is to determine feasibility of conducting a lifestyle modification intervention in a population of men with prostate cancer on ADT. This will be determined by calculating the study initiation rate, retention rate, and adherence rate. The study initiation rate will be calculated by dividing the total number of subjects that passed screening by the number started in the study after appropriate informed consent procedures. Retention rate will be calculated by dividing the total number of participants initiated by total number of participants in the study at 12 and 24 weeks. Retention goal for this trial is 80%, and hence participation 24 subjects in the trial at 12 and 24 weeks will satisfy this goal. The adherence rate hypothesized for this study is 75%. Participants will be determined to be adherent if they attend 75% intervention sessions (in-person and telephone intervention sessions combined). The overall adherence and retention rates and the associated 95% confidence intervals will be reported at 12 and 24 weeks. The secondary aim of this project to detect the effect of lifestyle modification on cardiometabolic risk factors and QoL. The tertiary aim of this project is to determine the effect of lifestyle modification on markers of inflammation and angiogenesis. Baseline characteristics will be described using mean and standard deviation for continuous variables and frequency and the associated proportions for categorical variables. Each outcome, for the secondary and tertiary aims, will be measured at 3 time points (ie, baseline, 12 weeks, and 24 weeks). For each outcome, two-sided 95% confidence intervals will be constructed for changes from baseline at both 12 and 24 weeks. In addition, a linear mixed-effects models will be fitted to explore the trajectory of changes overtime. If necessary, baseline value of the marker of interest (eg, cardiometabolic markers and QoL for secondary aim and inflammatory and angiogenic markers for the tertiary aim), age, race, serum prostate-specific antigen (PSA), and Gleason score will be adjusted for in the mixed-effects models. The changes in each of the outcomes over time will allow us to evaluate whether lifestyle modification can improve cardiometabolic risk and QoL (secondary aim) as well as inflammation and angiogenesis (tertiary aim). Analysis will be carried out using intent-to-treat (all participants) and modified intent-to-treat (restricting the analyses to participants who were adherent) approaches in order to determine if study adherence plays a role in mediating the relationship between lifestyle modification and outcome variables. Exit surveys will be carried out at the end of the study or if the participant decides to drop out of the study early. These qualitative and quantitate surveys will help understand participant satisfaction with the intervention and its delivery modalities, which will be helpful in planning the next phases of this project.

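### The formulas for the initiation and retention rates are written upside down and contradict the protocol's own retention goal of 24 out of 30

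*Protocol article*

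**What the plan says.** The Statistical Analysis section of the protocol article names three statistics for the primary aim of feasibility: "This will be determined by calculating the study initiation rate, retention rate, and adherence rate". It then gives formulas for the first two.

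- Initiation: "The study initiation rate will be calculated by dividing the total number of subjects that passed screening by the number started in the study" (consent having been given first).
- Retention: "Retention rate will be calculated by dividing the total number of participants initiated by total number of participants in the study", to be evaluated once for each of the two follow-up visits.

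The sentence directly after the retention formula states the goal: "Retention goal for this trial is 80%, and hence participation 24 subjects in the trial at 12 and 24 weeks will satisfy this goal". The Feasibility Measures section gives the same goal as a fraction: "If 80% (24/30) of participants complete the trial, the retention goal for this trial will be achieved". The planned sample is 30 men (Study Design). The Sample Size and Power section adds that, with 30 men, the two-sided 95% confidence interval for retention will be at most 0.374 wide at each follow-up visit.

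**The concern.** Dividing A by B means A/B. In both formulas A is the parent group (men who passed screening; men initiated) and B is the part of that group that went on (men who started; men still in the study). Each formula is therefore the reciprocal of the rate it names.

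These rates are main outputs of a feasibility study whose results are meant to inform later trials. An analyst who programs the definitions literally would report retention above 100% whenever anyone drops out, would see it rise as dropout worsens, and could not sensibly set it against an 80% goal. A reader would also find two opposite conventions for the same rate in adjoining sentences.

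**Working it through.** **Inputs**

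- Number initiated: 30, taking the recruitment target as reached (Study Design).
- Retention goal: 80%, equated with 24 men (Statistical Analysis) and with 24/30 (Feasibility Measures).
- Maximum 95% interval width for retention: 0.374 (Sample Size and Power).

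**Step 1: reproduce the 80%.** With 24 of 30 men retained:

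- formula as written, initiated / retained: 30/24 = 1.25 = 125%, which is not the stated figure;
- reciprocal, retained / initiated: 24/30 = 0.80 = 80%, which is.

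**Step 2: behaviour over the range of outcomes, 30 initiated.**

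| Retained | As written (30/retained) | Retained/30 | Head count of 24 reached? |
|---|---|---|---|
| 30 | 100% | 100% | yes |
| 27 | 111% | 90% | yes |
| 24 | 125% | 80% | yes |
| 23 | 130% | 76.7% | no |
| 20 | 150% | 66.7% | no |
| 15 | 200% | 50% | no |
| 10 | 300% | 33.3% | no |

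The men retained are a subset of those initiated, so the written ratio has its minimum, 100%, when nobody leaves. It grows with every dropout and is undefined if nobody remains.

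**Step 3: initiation.** The article gives no number passing screening, so one must be assumed. If 40 pass and 30 start, the written formula gives 40/30 = 133% and its reciprocal 30/40 = 75%. Over an assumed range of 30 to 60 passing, the written formula runs from 100% to 200%, and the reciprocal from 100% down to 50%.

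**Step 4: which orientation the precision statement assumes.** For a proportion with n = 30, the widest two-sided 95% interval occurs at 15/30. By method:

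- exact (Clopper-Pearson): 0.313 to 0.687, width 0.3741;
- Wald: 0.358;
- Wald with continuity correction: 0.391;
- Wilson: 0.337.

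Only the exact interval gives 0.374. The sample size section therefore treats retention as an ordinary proportion out of 30, which is retained over initiated.

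**Step 5: the goal in the corrected orientation.** 24/30 = 80.0% meets it, with exact 95% interval 61.4% to 92.3% (width 0.309). 23/30 = 76.7% misses it.

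**The case against.** The strongest reply is that nobody would be misled. The goal is stated twice as a head count, once in the sentence right after the faulty formula, and the interval width independently points to a proportion. The sentences read like a slip in the order of the two terms. Sample size, data collection and the count needed for success do not depend on them, and initiation has no threshold, so its inversion cannot change a feasibility decision. All of this stands and limits the consequence. It does not make the definitions right: they are the only formulas the article gives for these rates, both are inverted, and they disagree with the article's own 80%. Nor is this detail left to a fuller document, since the formulas are stated explicitly.

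Three stronger readings might be inferred. The article does not support them.

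- *That the 80% goal can never be missed.* This is true only of the ratio taken literally and set against 80%. Under the stated count of 24, any result of 23 or fewer retained misses the goal.
- *That no confidence interval can be formed.* The planned width matches an exact interval for a proportion. Even the reciprocal has an interval, obtained by inverting the limits: at 24/30, 1/0.923 = 1.08 to 1/0.614 = 1.63.
- *That recruitment lacks a statistic and initiation lacks a goal.* Thirty men recruited within six months is already a count in a fixed window, and an initiation rate without a threshold is a legitimate descriptive measure.

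**Conclusion.** The point holds as an error of definition. Two of the three rates named for the primary aim are written as their reciprocals. At the goal itself the written retention formula returns 125% where the article says 80%; at 20 of 30 it returns 150% where the proportion is 66.7%. The retention figures assume that 30 men are initiated. The floor of 100% assumes only that men who start come from those who passed screening, and that men still in the study come from those initiated. The initiation percentages rest on assumed screening numbers and are illustrative.

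The intended orientation can be recovered from the head count and the interval width, so the design and the success criterion are unaffected. The adherence rate is not touched by this point. The definitions should still be corrected before the feasibility results are computed and reported, because they specify the primary-aim statistics.

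**What to change.** Reword the two definitions in the Statistical Analysis section:

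- initiation rate = number started after consent / number that passed screening;
- retention rate = number in the study at week 12 / number initiated, and likewise at week 24, with the same denominator at both visits.

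State that the 95% interval for retention is the exact binomial interval, which is what the 0.374 width implies. The 80% goal then agrees with 24 of 30 throughout the article. The cost is a change of wording, carried into the analysis plan and code if they repeat these formulas. No new data, visits or sample size are needed.

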### Strengths and Limitations

The strengths of this study lie in its application of an evidence-based and effective multicomponent lifestyle modification intervention. This intervention has been successfully adapted for other disease types including breast cancer with favorable results. The standardized intervention with proven success in multiple disease settings, including cancer, sets this study apart from other comparable studies in current literature. The limitations of this study include its non-randomized treatment assignment and lack of a control group. Since this is a feasibility study, this is an accepted study design and a randomized study with an appropriate control arm would be the next step based on the study results.

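### The modified intent-to-treat analysis is an adherent-only set, and in a single-arm trial it cannot show whether adherence mediates the effect

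*Protocol article*

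**What the plan says.** The protocol article, under Statistical Analysis, names two analysis sets: "Analysis will be carried out using intent-to-treat (all participants) and modified intent-to-treat". The second is defined, and its purpose given, as "modified intent-to-treat (restricting the analyses to participants who were adherent) approaches in order to determine if study adherence plays a role in mediating" the relation between the intervention and the outcomes.

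The same section defines the subset: "Participants will be determined to be adherent if they attend 75% intervention sessions", with in-person and telephone sessions counted together. Feasibility Measures gives the same rule: "If participants attend 75% of the intervention delivery visits (in-person and phone combined), they will be considered adherent to the protocol". Adherence is also an endpoint of Aim 1, because "the outcome measures for this aim will be recruitment, retention, and maintaining protocol adherence by the participants".

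Study Design describes "a single-arm unblinded clinical trial". Strengths and Limitations concedes the consequence: "The limitations of this study include its non-randomized treatment assignment and lack of a control group".

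Efficacy Measures makes preliminary efficacy depend on significant changes over 24 weeks. It does not say which of the two sets decides.

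**The concern.** There are three separate problems.

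1. **Label.** Intent-to-treat, modified or not, suggests a set that is protected against selection by what happens after enrolment. A set chosen on attendance during the intervention has no such protection.
2. **Inference.** Mediation concerns how an exposure produces its effect, so it needs a contrast in exposure. Here every man is offered the intervention, so the intervention–outcome relation that adherence is meant to mediate is not itself identified.
3. **Selection.** Attendance may be related to how a man is doing. If men who lose weight or feel better tend to keep attending, the subset shows a better mean change than the cohort for reasons unrelated to any effect of the programme.

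What is at stake is the reading of the efficacy results. Because no set is named for the preliminary-efficacy judgement, the adherent-only result is available for it. A gap between the two sets could also be carried into the design of the next trial as evidence that the programme works in men who adhere.

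**Working it through.** The plan states no figure for this analysis, so there is none to reproduce. The check has two parts.

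**Part 1: what the comparison measures.** Let q be the share of men who are adherent, and let A and N be the mean changes in adherent and non-adherent men. With complete outcome data the all-participant mean is qA + (1 − q)N, so

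adherent-only mean − all-participant mean = A − qA − (1 − q)N = (1 − q)(A − N).

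At q = 0.75 the gap is 0.25 × (A − N). Setting the two analyses side by side is therefore a diluted comparison of attenders with non-attenders, all of whom were offered the same intervention. It has no untreated contrast and so carries no information on mediation.

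**Part 2: how large a gap selection alone can produce.** Inputs:

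- n = 30 (Sample Size and Power).
- q = 0.75. Statistical Analysis hypothesizes a 75% adherence rate; reading that as the share of adherent men is an assumption.
- True mean change = 0, set for the check.
- r, the correlation between attendance propensity and favourable change. The documents give no value, so a range is shown.

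If attendance propensity and change are bivariate normal and the top share q counts as adherent, the expected change in adherent men, in SD of the change, is

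r × φ(z) / q, with z the (1 − q) quantile of the standard normal.

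At q = 0.75, z = −0.674, φ(z) = 0.318, and φ(z)/q = 0.424. For example, at r = 0.3 the result is 0.3 × 0.424 = 0.127.

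The other columns come from 40,000 simulated trials of 30 men per value of r, with no missing outcomes. The test is a one-sample t-test at two-sided 5%, and the favourable direction is counted.

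| r (assumed) | Apparent mean change, adherent only (SD of change) | Falsely significant favourable, adherent only | Adherent-only mean exceeds all-participant mean |
|---|---|---|---|
| 0 | 0.00 | 2.5% | 50% |
| 0.2 | 0.085 | 5.9% | 79% |
| 0.3 | 0.127 | 8.1% | 89% |
| 0.5 | 0.21 | 17.0% | 98% |
| 0.7 | 0.30 | 32.9% | 99.9% |

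In all 30 men the false favourable rate stays near 2.5% at every r.

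The result depends on q. If 60% of men are adherent, r from 0.2 to 0.7 gives 0.13 to 0.45 SD, and false favourable rates of 7.5% to 56.7%.

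**The case against.** The strongest reply is that the plan is open about what it does and that little hangs on it. The restriction to adherent men is spelled out beside the label. The all-participant analysis is kept. The outcomes affected are secondary and tertiary in a feasibility trial of 30 men, and the primary aim is untouched. The article lists the missing control group as a limitation and names a randomized study as the next step. All of this stands and limits the impact. It does not rescue the stated purpose, which is a mediation question that the design cannot answer.

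Mediating may also be meant loosely, as asking whether adherence matters. Part 1 of the working applies to that reading too: attenders and non-attenders can differ for reasons other than the dose of intervention they received.

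Three stronger conclusions that a reader might infer are not supported:

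- *The subset is bound to look favourable.* This requires a positive attendance–change correlation. At r = 0 there is no bias, and a negative correlation would make the subset look worse. Can is the right word.
- *The subset is nearly the completers, because nobody leaving before about week 18 can qualify.* Week 18 is 0.75 × 24 and assumes that all 24 weekly contacts count. The Abstract and the Intervention section describe a 16-week curriculum followed by 8 weeks of support calls. If only the 16 sessions count, the threshold is 0.75 × 16 = 12.
- *The bias is a given fraction of the 0.47 SD detectable change.* Sample Size and Power does not say whether that SD is of the raw measurement or of the change, so the ratio is not defined.

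The calculation also assumes every man has an outcome. If men who leave have no week-24 measurement, the observed all-participant data at week 24 come largely from the same men as the subset, and the visible gap would be smaller than shown.

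**Conclusion.** The concern holds in a limited form. Two parts do not depend on any numerical assumption: the set is selected on a post-baseline Aim 1 outcome, so it is adherent-only and not intent-to-treat; and in a single arm, comparing it with the cohort that contains it cannot identify mediation.

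The third part is conditional. With no true effect, q = 0.75 and r between 0 and 0.5, the apparent mean change runs from 0 to 0.21 SD of change, and the false favourable rate from 2.5% to 17%. These figures rest on an assumed r, on bivariate normality, on complete outcome data, and on reading the hypothesized 75% as the share of adherent men. They show what selection can do, not what will happen in this trial.

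The text should be corrected because it fixes a method to a conclusion the method cannot give. The retained all-participant analysis and the secondary and tertiary status of the outcomes keep the matter below the level of a threat to the trial's primary aim.

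**What to change.** - In Statistical Analysis, rename the second set adherent-only (per-protocol, at least 75% attendance), exploratory.
- Delete the statement that comparing the two sets determines whether adherence mediates the relationship.
- In Efficacy Measures, state that the all-participant analysis decides preliminary efficacy.
- If adherence is to be examined, report number of sessions attended against change, in all men with available outcome data, as an association with a 95% confidence interval and with no causal or mediation claim. This analysis is open to the same reverse causation (men doing well may attend more), so it describes the data and does not cure the problem.

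The cost is a small rewording and one simple additional analysis on data already being collected. No change to sample size, visits or assessments is needed.
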